## Abstract

**Background:**

People with Parkinson disease (PD), even in the presence of symptomatic relief from medical, surgical, and rehabilitative interventions, face a persistent worsening of disability. This disability is characterized by diminished quality of life, reduced functional mobility, declining performance in activities of daily living and worsening neurological impairments. While evidence has emerged supporting the clinically meaningful benefits of short-term exercise programs on these underlying factors, assertions regarding the effects of sustained programs of exercise and physical activity on the trajectory of disablement in PD are made in the absence of direct evidence. Indeed, the natural decline in quality of life and functional mobility in people diagnosed with PD is poorly understood. Moreover, outcome measures commonly used in clinical exercise trials typically do not capture the full spectrum of disability as defined by the World Health Organization (WHO).

**Methods/Design:**

The objective of this multicenter prospective study will be to examine the 2-year trajectory of disablement in a cohort of persons with PD. Two hundred sixty participants will be recruited to produce an expected final sample size of 150 individuals. Participants will be included if they are greater than 40 years of age, have a neurologist confirmed diagnosis of idiopathic PD, and are at Hoehn and Yahr stages 1 through 4. Data will be collected every 6 months during the study period. Primary outcome measures reflecting a broad spectrum of disablement will include, but will not be limited to, MDS-UPDRS, Timed Up and Go, Berg Balance Test, Nine Hole Peg Test, PDQ-39, and directly monitored ambulatory activity. Self-reported exercise and physical activity data also will be recorded. Statistical analyses will be used to characterize the trajectory of disablement and examine the influence of its underlying contributing factors.

**Discussion:**

Tertiary prevention is an important component of contemporary healthcare for individuals living with degenerative disease. For individuals with PD, there is growing recognition that exercise and/or physical activity efforts to slow the rate of functional mobility decline, in particular, may be critical for optimizing quality of life. By describing the natural trajectory of disablement, exercise habits, and physical activity in a cohort of persons with PD, this investigation will establish an important foundation for future intervention research. Specifically, through the evaluation of the influence of sustained exercise and physical activity on disablement, the study will serve as a preliminary step toward developing a randomized controlled trial of long-term exercise in persons with PD.

## Background

Parkinson disease (PD) is a chronic, progressive neurodegenerative disease affecting more than 4 million people world-wide[1]. With adequate access to healthcare services, persons with PD can live 20-30 years following initial diagnosis[2]. Nonetheless, persons with PD face a persistent deterioration in functional mobility and activities of daily living often resulting in a loss of independence and a decline in quality of life.

Over the last decade, a growing body of evidence has emerged revealing significant and clinically meaningful benefits of exercise for addressing PD-related problems. For example, a critical review of the literature identified 23 randomized controlled trials demonstrating that patients who participated in exercise programs had better quality of life, walking ability, balance, strength, flexibility and cardiovascular fitness compared to those who did not exercise[3]. Exercise studies of both rodent and primate models of PD have demonstrated increased survival of nigrostriatal dopaminergic neurons, suggesting a potential protective effect of exercise as well[4,5]. Furthermore, a prospective epidemiological study revealed a significant decreased risk of developing PD in people who participated in moderate to vigorous exercise[6,7].

Although promising, studies of exercise in PD have been limited in scope. Most have examined the effects of short-term exercise programs, typically implemented over 4 to 12 weeks. Furthermore, in studies with prolonged follow-up, exercise benefits typically attenuated over weeks to months following the intervention period[8,9]. Thus, the benefit of longer, more sustained patterns of regular exercise on PD-related problems remains poorly understood. In particular, the impact of sustained exercise and/or a physically active lifestyle on the rate at which persons with PD become disabled (i.e., the "trajectory of disablement") remain unknown.

Currently the Unified Parkinson Disease Rating Scale (UPDRS) and its most recent version (the MDS-UPDRS) are considered the gold standards for examining disease severity and progression[10-12]. The UPDRS focuses primarily on measuring impairments associated with PD, with fewer items addressing specific functional limitations or perceptions of quality of life. The subsections of the UPDRS are organized according to motor and non-motor aspects of the disease, significantly limiting the assessment of disablement in PD. As a result, the burden of PD is commonly understood more in terms of disease progression (i.e., the predictable evolution of signs, symptoms, and impairments) rather than in terms of the potentially diverse paths through which persons with PD become disabled.

In contrast to the UPDRS, the International Classification of Functioning, Disability, and Health (ICF) was developed as a framework for understanding disability at multiple levels[13]. Accordingly, the effect of health conditions (e.g., PD) is considered across 3 domains of human function: body structure and function, activity, and participation. "Disability" is used to denote a decrement at each level (i.e., a body structure or function impairment, an activity limitation, and a participation restriction)[13]. Underscoring the value of this approach, the World Health Organization (WHO) endorsed the ICF in 2001[14].

"Body structure," in ICF terms, is defined as an anatomical part of the body, such as organs, limbs and their components, while "body function" is defined as the physiological function of body systems. Applied to PD, motor signs such as bradykinesia, tremor and rigidity represent impairments in body structure and function. "Activity" is defined as the execution of a task or action by an individual and activity limitations as the difficulties an individual may have in executing such tasks. Activity limitations common in PD are those affecting gait, balance, getting dressed, bathing, and other activities of daily living. Lastly, "participation" is defined as the involvement in a life situation and participation restrictions as problems an individual may experience in involvement in life situations. Participation restrictions in PD may include involvement in leisure, work or social aspects of life in both the household and community settings[14].

To address the aforementioned limitations in the exercise and disability literature, we plan to conduct a 2-year, multicenter prospective longitudinal study of a cohort of persons with PD. The objectives of the study will be: (1) to characterize the natural trajectory of disablement using a spectrum of measures organized according to the ICF framework, and (2) to identify potential factors, including but not limited to those related to exercise and physical activity, that contribute to the development of impairments of body structure/function, activity limitations, or participation restrictions. The study is anticipated to lay an important foundation for future studies, especially those designed to understand the impact of sustained exercise and/or a physically active lifestyle on disablement in PD.

## Methods/Design

### Research Design

The proposed project is a prospective, longitudinal cohort study in which patients with PD will be assessed every 6 months over a 2-year period using a specific battery of outcome measures designed to reflect the full spectrum of disability.

### Participants and Recruitment

Two hundred sixty participants will be recruited through the Neurology Department at the University of Utah, the Parkinson's Disease and Movement Disorder Center at Boston University Medical Center (BU PDMC), the Department of Neurology at the University of Alabama at Birmingham (UAB), and the Movement Disorders Center at Washington University in St Louis School of Medicine. Prior to data collection, ethics approval will be achieved through the Institutional Review Board (IRB) at each participating site. Before participation, all participants will sign IRB approved informed consent forms. Gathering data at four sites will promote rapid enrollment and increase the likelihood of enrolling participants who typically are under-represented in PD studies (e.g., Ethnic minority participants, females, individuals who are at Hoehn and Yahr Stage 4). Included participants will be community dwelling persons ≥ 40 years of age who have neurologist-diagnosed idiopathic PD (using UK Brain Bank Criteria [15]), are at Hoehn and Yahr stages I-IV (mild to moderate disease severity), and score ≥ 24/30 on the Mini-mental State Examination. Excluded participants will be individuals with a diagnosis of atypical Parkinsonism, who are at Hoehn and Yahr stage 5, or who have had previous surgical management of PD (e.g. pallidotomy, deep brain stimulation).

### Power and Sample Size Estimates

A 25% annual attrition rate is anticipated over the 2-year study period, resulting in a final estimated sample size of 150 participants. The final sample will be sufficient to provide precise disability estimates and to allow for the inclusion of as many as 12 predictor variables in multiple regression analyses that evaluate the underlying contributors to various trajectories of disablement (α = 0.05; N ≥ 50 + 8 (X), where X = the number of predictor variables.)[16]

### Procedures

At baseline, demographic information and disease history will be collected via interview. At each measurement interval (i.e., baseline, 6 months, 1 year, 1.5 years and 2 years), (1) co-morbidity data will be collected using a modified version of the Comorbidity Questionnaire, a reliable and valid instrument that offers practical advantages over medical record based assessments [17]; (2) depression will be assessed using the Geriatric Depression Scale [18,19]; and (3) medication data (i.e., drug name, dose, frequency, levo-dopa equivalence) will be collected using a customized form. In addition, a suite of standardized instruments will be employed at each measurement interval to capture participant physical function, mobility, physical activity, and quality of life. The instruments have been selected for their strong psychometric properties and collective representation of ICF domains (Table 1 and Figure 1)

**Table 1 T1:** Battery of Outcome Measures

ICF Disablement Construct	Outcome Variable
Body Structure and Function	
	MDS-UPDRS Sections I, III

Activity	
	6 Minute Walk Test
	9 Hole Peg Test
	Berg Balance Scale
	Freezing of Gait Questionnaire
	Functional Gait Assessment
	Gait Speed (10 meter walk)
	MDS-UPDRS Section II
	Timed Up and Go

Participation	
	Ambulatory Activity
	PASE
	PDQ-39

MDS-UPDRS = Movement Disorders Society-Unified Parkinson Disease Rating Scale; PASE = Physical Activity Scale for the Elderly; PDQ-39 = Parkinson Disease Questionnaire - 39

**Figure 1 F1:**
[figure not shown]
**Flow sheet of Study Procedures**. Abbreviations: UAB = University of Alabama at Birmingham, MDS-UPDRS = Movement Disorders Society-Unified Parkinson Disease Rating Scale, FOG-Q = Freezing of Gait Questionnaire, PDQ-39 = Parkinson Disease Questionnaire - 39, PASE = Physical Activity Scale for the Elderly.

### Measure of Body Structure and Function

Sections I and III of the MDS-UPDRS will be utilized to assess neurological signs[10,12]. Section I, which is entitled "Non-motor aspects of experiences of daily living", consists of 13 items that will be administered via clinician interview and a participant/caregiver questionnaire. Section III consists of 18-items pertaining to motor aspects of the disease, the data for which will be obtained by examining the participant at the time of each visit. Each item is rated on a 5-point (0-4) ordinal scale, with higher scores indicating more severe impairment.

### Measures of Activity

(1) Section II of the MDS-UPDRS consists of 13 items related to activities of daily living (ADL). Data will be obtained via interview. Each item is rated on a 5-point (0-4) ordinal scale with higher scores indicating more severe activity limitation. The UPDRS has been administered in several large clinical trials in PD and is reliable, valid and responsive to change[10,12].

(2) The Berg Balance Scale (BBS) is a 14-item test battery that quantitatively assesses balance and risk for falls through direct observation of performance[20]. The BBS requires approximately 15 minutes to complete and measures the participant's ability to maintain balance either statically or dynamically over a specified period of time[21]. The items are scored on a 5-point (0-4) ordinal scale. The total score, which will be used as the dependent variable, ranges from 0 to 56 with higher scores indicating better balance. Validity and high test-retest reliability of the BBS total score have been demonstrated across a variety of populations including patients with PD[22,23].

(3) The Functional Reach Test (FR) measures the maximum distance a participant can reach in the forward direction with a fixed base of support[24]. Each participant will be asked to make a fist, raise the dominant arm parallel to the floor and reach as far forward as possible without taking a step. Using a yardstick mounted on the wall at the shoulder height and the third metacarpal as the reference point, the distance between the starting and ending position will be recorded. Two practice trials and 3 test trials will be conducted, with the mean distance reached during the 3 test trials used as the dependent variable. Validity and high test-retest reliability of the FR have been established in healthy elders and in people with PD [23,24].

(4) The Functional Gait Assessment (FGA) is a 10-item standardized test for assessing postural stability during various walking tasks. Items include walking with head turns, walking with eyes closed, walking while altering gait speed, walking in a backward direction, walking with a narrowed base of support, negotiating obstacles, stopping, turning and stair climbing. Items are scored using a 4-point ordinal scale (0-3). Total score, which will be used as the dependent variable, ranges from 0 to 30, with higher scores indicating better performance. Reliability, internal consistency and validity of the FGA total score have been established in healthy adults and in patients with neurological disorders[25,26].

(5) The six-minute walk (6MW) test, a measure of the distance a participant walks in 6 minutes, will be used to assess overall locomotor ability. The 6MW distance is related to functional movement tasks and is an independent predictor of prognosis in older patients with co-morbid conditions. The 6MW's test-retest reliability is high, ranging from .94 - .96, in older populations with various co-morbid conditions[23,27].

(6) Self-selected and maximal pace gait speed will be measured during a 10 meter walk. Three trials at each pace will be recorded, with the average speed at each pace used as separate dependent variables. Gait speed provides a standardized measure of gait function that has been found to be reliable and is sensitive to change over a broad range of physical function in elderly individuals and persons with neurologic pathology[23,27,28].

(7) The Freezing of Gait Questionnaire (FOG-Q) is a valid and reliable 6-item tool used to assess the severity of freezing of gait in patients with PD[29,30]. Each item is rated on a 5-point ordinal scale, from 0 (absence of symptom) to 4 (most severe symptom). The total score, which will be used as the dependent variable, reflects the sum of the 6 items and ranges from 0-24. The FOG-Q will be self-administered by all participants.

(8) The "Timed Up and Go" Test (TUG) measures the time it takes for a participant to stand from a seated position in an armchair, walk forward 3 m at a comfortable pace, turn around, walk back to the chair, and sit down. Each participant will perform a practice trial followed by 2 test trials. The mean of the 2 test trials will be the dependent variable. In older adults at risk for falls, the TUG has been found to possess excellent intra and inter-tester reliability (.94-.96) and predictive validity in that increased times on the TUG relate to increased fall-risk[23,31,32].

(9) The Nine Hole Peg Test (9-HPT) is a brief, standardized, quantitative test of upper extremity function that asks the participant to place and remove nine pegs one at a time, as quickly as possible, from nine holes in a peg board. Scoring is determined by the total time to complete the task. Two trials with the dominant hand will be immediately followed by two trials with the non-dominant hand. The mean of the two trials for each hand will be the dependent variable. The 9-HPT has high inter-rater reliability and good test-retest reliability. There is evidence for concurrent and convergent validity as well as sensitivity to detect minor impairments of hand function[33,34].

### Measures of Participation

(1) The Parkinson's Disease Questionnaire-39 (PDQ-39) is a health status instrument that contains 39-self-report items and was specifically developed for people with Parkinson's disease. The PDQ-39 measures the degree of healthy, competent, and satisfying participation in daily life activities. The reliability, validity, and sensitivity to change of the PDQ-39 have been established in community dwelling persons with PD. In addition to the composite summary score, we will utilize the 8 subscores (i.e., mobility, activities of daily living, emotions, stigma, social support, cognition, communication, and body discomfort) to reflect constructs that have been consistently found to contribute to perceived quality of life in persons with PD)[35-37].

(2) Ambulatory Activity: To capture "free-living" ambulatory activity, a sub-group of participants will wear a StepWatch 3 Activity Monitor (SAM, Orthocare Innovations, Seattle, WA,), 24 hours per day for 7 consecutive days, except when bathing, showering, or swimming. The SAM is approximately the size of a pager, weighs 38 g, and is attached using Velcro closures immediately proximal to the lateral malleolus of either leg. The SAM uses a combination of acceleration, position, and timing to detect steps taken by the leg on which it is worn. It is designed for long-term use during daily activities performed in an individual's customary environment over hours or days without maintenance by the user. Data are recorded as a temporal series of counts, with each data point representing the number of steps per one-minute interval. Data will be downloaded to a personal computer via an infrared docking station and post processed using either manufacturer software or custom analysis programs written in Matlab (Mathworks, Natick, MA). Step counts will be used to generate multiple indices of mean daily ambulatory activity (e.g., total number of steps, percent of day spent inactive, total number of bouts of activity, bout duration, and activity intensity). The SAM is particularly accurate for individuals with impaired gait, is unobtrusive and easy to use, and has demonstrated good test-retest reliability (ICC, r = 0.84) and accuracy (98%) in an older adult population[38-42].

(3) The Physical Activity Scale for the Elderly (PASE) measures the level of self-reported physical activity in individuals aged 65 years or older and is comprised of items regarding occupational, household, and leisure activities during the previous 7-day period[43,44]. Leisure activities include frequency and duration of walking outside the home, as well as participation in light, moderate and strenuous exercise. The total PASE score, which will be used as the dependent variable, is computed by multiplying the time spent in each activity (hours/week) or participation (yes/no) in an activity by empirically derived item weights and summing over all activities. The PASE has previously been validated in elderly populations[45-47].

### Statistical Analysis Plan

Confidence intervals, means, standard deviations and frequency distributions will be calculated for all measures. Corrections for multiple comparisons will be used to control for increased type I statistical error risk. Effect sizes and post hoc power will be calculated when appropriate. All analyses will be performed with SPSS 16.0 (SPSS Inc).

To address study objective 1, disablement trajectory will be characterized using interval and point estimators of each outcome measure. In addition, survival analyses will be utilized to examine the time to reach operationally defined mobility thresholds (i.e., limited community ambulatory gait speed, assistance with ADL's, time to recurrent falls). This approach will allow us to characterize the distribution of time-to-event data, to test for differences between subgroups (i.e., exercise history, disease severity, disease sub-type, age, number of cormorbidities), and to utilize regression models to analyze complex influences of covariates on time to event data[16].

To address study objective 2, multiple regression analyses will be conducted to identify those factors associated with progression of disability. Assessments for violation of assumptions will be made, including analyses of normality of the residuals and linearity of the continuous variables[16]. As needed, potentially more potent contributors will be used to define subgroups within the sample (e.g., exercisers vs. non-exercisers; physically active vs. sedentary), and analyses of variance will be used to evaluate between- and within-group differences in disablement change.

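### Post hoc power is planned with no effect named to evaluate it at; computed at the observed effect, it only re-expresses the p-value and degrees of freedom

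*Protocol article*

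**What the plan says.** In the protocol article, the opening paragraph of the Statistical Analysis Plan commits to the calculation in one sentence: "Effect sizes and post hoc power will be calculated when appropriate". It does not say when the calculation is appropriate, which tests it covers, or whether the effect used is the observed one or one fixed beforehand.

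The same paragraph plans intervals: "Confidence intervals, means, standard deviations and frequency distributions will be calculated for all measures". It also plans corrections for multiple comparisons.

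The tests to which post hoc power could attach are the survival comparisons and regressions under objective 1, the multiple regressions under objective 2, and subgroup comparisons, for which "analyses of variance will be used to evaluate between- and within-group differences in disablement change".

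Power and Sample Size Estimates justifies the sample by a rule of thumb ("α = 0.05; N ≥ 50 + 8 (X), where X = the number of predictor variables"), which is said to allow "inclusion of as many as 12 predictor variables in multiple regression analyses". That section states no effect to be detected and no power value.

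**The concern.** A power figure is informative when it refers to an effect chosen without looking at the data. Evaluated at the effect just estimated, it is the p-value on another scale. A reader who sees low power beside a non-significant exercise or activity factor may conclude that the study could not have found anything, even where the confidence interval excludes an effect of useful size. A reader who sees high power beside a non-significant multi-parameter test may conclude that absence has been shown.

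Objective 2 is to identify contributing factors, including exercise and physical activity, and the article presents the study as groundwork for a randomised trial of long-term exercise. What is at stake is how null findings on those factors are read.

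**Working it through.** **Inputs.** Alpha 0.05, final N = 150 and up to 12 predictors come from Power and Sample Size Estimates; 260 recruited comes from Participants and Recruitment. Two-sided testing is assumed, because sidedness is not stated.

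**The plan's own figures.**
- Attrition: 260 × (1 − 0.25)² = 146.25, within 3% of the stated 150.
- Predictors: (150 − 50)/8 = 12.5, so 12; and 50 + 8 × 12 = 146.

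These reproduce and are not in question. They contain no effect size and no power, so the section supplies nothing at which a later power calculation could be evaluated.

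**One-degree-of-freedom tests** (a single predictor or a two-group contrast). Let z_p be the normal quantile at 1 − p/2. Observed power = Φ(z_p − 1.96) + Φ(−z_p − 1.96).

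| p | z_p | Observed power |
|---|---|---|
| 0.05 | 1.960 | 0.500 |
| 0.10 | 1.645 | 0.376 |
| 0.20 | 1.282 | 0.249 |
| 0.50 | 0.674 | 0.104 |

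N does not enter the formula. With the noncentral t at 20, 75 and 130 per group, the values are 0.505, 0.501 and 0.501 at p = 0.05; 0.246, 0.249 and 0.249 at p = 0.20; and 0.102, 0.103 and 0.103 at p = 0.50.

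**What this does to a tight interval.** Assume a 75 versus 75 split (the article gives no group sizes).
- The 95% half-width is 1.96 × √(2/75) = 0.32 SD.
- Power for a difference of 0.5 SD, chosen here only for illustration, is 86%.
- A result with p = 0.50 has an estimate of 0.674 × √(2/75) = 0.11 SD, so an interval of about −0.21 to 0.43 SD. This excludes 0.5 SD.
- Observed power for the same result is 10%.

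The interval shows that the comparison was informative about 0.5 SD; the power figure suggests that it was not.

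**Multi-degree-of-freedom F tests at N = 150.** Observed power is the probability that a noncentral F, with noncentrality df1 × F_obs, exceeds the 5% critical value.

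| df | p = 0.05 | p = 0.10 | p = 0.20 |
|---|---|---|---|
| 2, 147 | 0.58 | 0.47 | 0.34 |
| 3, 146 | 0.64 | 0.53 | 0.41 |
| 12, 137 (overall test of 12 predictors) | 0.87 | 0.81 | 0.72 |

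For the last row at p = 0.10, F_obs = 1.594, the noncentrality is 12 × 1.594 = 19.13 and the critical value is 1.823, which gives 0.81. The figure is again fixed by p and the degrees of freedom, but here it can look reassuringly high for a non-significant result.

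**An informative alternative.** For one predictor adjusted for 11 others, the partial correlation detectable at 80% power (assumed) is tanh[(1.960 + 0.842)/√(150 − 11 − 3)] = tanh(2.802/√136) = 0.236, about 0.24. This uses alpha 0.05 with no multiplicity correction; a correction would raise it.

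**The case against.** Four points can be made for the plan.

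1. **The article never says that the observed effect will be used.** Power at the achieved N for an effect fixed beforehand would not restate the p-value, and a condensed article may leave this detail to a fuller plan. This stands as a caveat: the observed-effect reading is an inference. It is the natural one, because no other effect is named and the sentence pairs post hoc power with calculated effect sizes.

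2. **The 50%-or-less pattern is not universal.** A reader might infer that every non-significant result would look underpowered. The planned tests do not support that. The analyses of variance and overall regression tests can have several degrees of freedom, and there observed power at p = 0.10 reaches 53% (3 df) or 81% (12 df). The low-power pattern belongs to one-degree-of-freedom tests. What carries over to the others is the redundancy. The figures also assume alpha 0.05, which the planned multiplicity corrections could change.

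3. **Intervals are already planned, and nothing says that null results will be excused as low power.** Both statements are correct, and such misuse should not be attributed to the investigators. But the interval commitment is worded for the outcome measures and does not explicitly reach regression coefficients, hazard ratios or group differences. A misleading number printed beside an interval is also not neutral.

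4. **Little depends on the phrase.** It is hedged, and no sample-size figure, main analysis or decision rule uses it. This stands in full and sets the priority.

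**Conclusion.** The concern holds within limits. The plan commits to a calculation whose reference effect is unspecified. On its usual meaning, the result is determined entirely by the p-value and the degrees of freedom. At two-sided alpha 0.05 it is 50%, 38%, 25% and 10% at p = 0.05, 0.10, 0.20 and 0.50 for one-degree-of-freedom tests, and 81% at p = 0.10 for a 12-predictor overall F test at N = 150. It therefore adds no information and can mislead in either direction, depending on the test.

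The conclusion rests on the observed-effect reading, two-sided testing and no adjustment of alpha. It does not call the sample size or the main analyses into question. Low priority.

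**What to change.** Delete the post hoc power half of the sentence and keep the effect sizes. State that regression coefficients, hazard ratios and group differences will be reported with confidence intervals, and that non-significant exercise and activity factors will be interpreted from those intervals.

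If the authors want to show sensitivity, they should state before analysis the effect detectable at N = 150 for the key exercise and activity factors: about a 0.24 partial correlation with 12 predictors, at an assumed 80% power and before any multiplicity correction. A minimal effect for every predictor and outcome is not needed.

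The cost is an edit to one sentence, somewhat more interval reporting and, if sensitivity is shown, one reference effect stated in advance. No useful information is lost.

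### With five visits planned and about 44% loss expected by 2 years, the outcome scores would be better analysed by a mixed model on all visits than by the estimators, regression and ANOVA named

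*Protocol article*

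**What the plan says.** Under Procedures, the battery is collected at baseline, 6 months, 1 year, 1.5 years and 2 years. Under Power and Sample Size Estimates, the expected loss is given: "A 25% annual attrition rate is anticipated over the 2-year study period, resulting in a final estimated sample size of 150 participants". The same section ties both aims to that number: "The final sample will be sufficient to provide precise disability estimates and to allow for the inclusion of as many as 12 predictor variables". The rule it uses is "α = 0.05; N ≥ 50 + 8 (X), where X = the number of predictor variables".

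The Statistical Analysis Plan section then names the methods.

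- **Objective 1:** "disablement trajectory will be characterized using interval and point estimators of each outcome measure". Survival analyses of the time to three kinds of threshold event (limited community gait speed, needing help with daily activities, recurrent falls) are added.
- **Objective 2:** "multiple regression analyses will be conducted to identify those factors associated with progression of disability". Where groups are later formed, such as exercisers against non-exercisers, "analyses of variance will be used to evaluate between- and within-group differences in disablement change".

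No mixed, growth-curve or other longitudinal model is named for the outcome scores. The section does not say who enters each analysis when visits are missing, and no sentence limits any analysis to those who complete 2 years.

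**The concern.** The trajectory of disablement is the main product of this study, and the repeated visits are its main asset. Means and intervals at each visit treat each visit as a separate sample. Ordinary multiple regression takes one value per person. Classical repeated-measures ANOVA drops anyone with a missing visit. With nearly half the cohort expected to leave, these methods estimate the cohort's trajectory without bias only if leaving is unrelated to disability.

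That is open to doubt here. The disease is progressive, Hoehn and Yahr stage IV is included, and follow-up depends on walking and balance tests. If the more disabled leave first, the people left at 2 years are fitter from the outset, and a plot of visit means will look flatter than the true course. For objective 2, visits already collected from people who leave could go unused.

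**Working it through.** **1. The plan's own figures.** Inputs: 260 recruited ("Two hundred sixty participants will be recruited to produce an expected final sample size of 150 individuals") and 25% annual loss.

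- Retention: 260 × 0.75² = 146.25, close to the stated 150. That is 56% of enrolment (58% if 150 is used), so about 44% are lost.
- Regression rule with 12 predictors: 50 + 8 × 12 = 146. The final sample just meets it.

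**2. Visits available.** Assume retention of 0.75^t at t years, with steady loss within each year.

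- Expected numbers seen: 260 + 225 + 195 + 169 + 146 = about 995 participant-visits.
- Completers, all five visits: 146.25 × 5 = 731. Unused: 1 − 731/995 = 27% (22% to 31%, depending on when in the year people leave).
- Completers, baseline and 2 years only: 146.25 × 2 = 292.5. Unused: 1 − 292.5/995 = 71% (69% to 72%).

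**3. Bias under severity-related dropout.** The article gives none of these inputs; all are assumed: higher score is worse, baseline (random intercept) SD 1, mean worsening 0.25 SD per year (0.50 over 2 years), slope SD 0.3 per year, residual SD 0.4. The log-odds of leaving before the next visit rise by 0, 0.5 or 0.8 per SD of the last observed score, with the intercept set so that 44% leave by 2 years.

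| Estimate of 2-year worsening (truth 0.50) | Log-odds 0 | 0.5 | 0.8 |
|---|---|---|---|
| Mean of those seen at 2 years minus baseline mean of all | 0.50 | 0.22 | 0.09 |
| Completers' own change | 0.50 | 0.48 | 0.46 |
| Mixed model, all visits (variance components taken as known) | 0.50 | 0.50 | 0.50 |

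The first two rows differ because completers start fitter. Their own baseline means are −0.26 and −0.37 in the last two columns: 0.22 + 0.26 = 0.48 and 0.09 + 0.37 = 0.46. To three decimals the first is 0.475, so the shortfall in completers' mean change is (0.50 − 0.475)/0.50 = 5%, and (0.50 − 0.46)/0.50 = 8%.

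**4. Precision under random dropout.** Same variances.

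- Completers' change per year: variance per person = 0.3² + 2 × 0.4²/2² = 0.09 + 0.08 = 0.17. SE = √(0.17/146.25) = 0.034.
- Mixed model: sum X'V⁻¹X over all 260, each with the visits they supply, where V = ZGZ' + 0.16·I and G has diagonal 1 and 0.09. The slope SE from the inverse is 0.030.

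**The case against.** **Completers only.** A reader might infer that every analysis rests on the 2-year completers. The document does not say so. Planning on the number left after attrition is ordinary caution and does not define an analysis set. The trajectory estimates could use everyone seen at each visit. This objection stands.

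**Repeated measures ignored.** A reader might also infer this, but it goes too far. The survival analyses use the serial visits and can censor people who leave, and the ANOVA has a within-group part. What remains is narrower: the survival analyses cover three threshold events and not the outcome scores.

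**Large bias and wasted visits together.** These belong to different readings. The 0.22 and 0.09 SD arise only when visit means use everyone seen and are set against the full baseline, and then no visits are discarded. The 27% arises only if change is analysed in completers, where the bias in the mean is 5% to 8%. The two cannot be added.

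**Decline is understated.** The document does not establish this. It gives no reasons for attrition and no rates by severity. If those who leave decline more slowly, the error reverses: were their decline 0.8 times that of completers, the completers' mean change would be 1/(0.5625 + 0.4375 × 0.8) = 1.10 times the cohort's.

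**Left to a fuller plan.** Analysis sets and missing-data rules are often left out of a protocol article, and their absence here is not held against it. But the article does itself choose the methods for the outcome scores and does itself justify precision on the final sample. That choice can be improved whatever a fuller plan adds.

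**Conclusion.** The point holds as a recommendation about method. For a five-visit study expecting about 44% loss, the named analyses of the outcome scores do not use a departing participant's own earlier visits to inform later scores, and a readily available method does.

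The cost depends on how the plan is carried out. With visit-wise means of everyone seen, more than half of a true 0.50 SD decline could be missed (0.22 or 0.09 SD shown) if dropout follows severity as assumed. With completers' change, the mean is nearly right (5% to 8% low), but 27% to 71% of visits are unused and the slope SE is about 0.034 against 0.030, even with random dropout.

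The simulated sizes rest on assumed variances and dropout strength. The mixed model's exact recovery also reflects the set-up, in which dropout depends only on observed scores. None of this shows that the planned results will be wrong or that the regression sizing fails its own rule. The point is a cheap improvement, not a must-fix error.

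**What to change.** For each approximately continuous outcome, make a linear mixed model the main analysis in place of the visit-wise means, multiple regression and ANOVA. Fit it to all available visits of all enrolled participants, with a random intercept and slope per participant, fixed effects for time and site, and each candidate factor entered with its interaction with time.

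- Objective 1: report model-based means at 0, 6, 12, 18 and 24 months, and the slope, with intervals.
- Objective 2: report the factor-by-time interactions.
- Keep the survival analyses as planned.
- Add one sensitivity analysis in which scores after dropout are shifted towards worse values.

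The cost is a change of wording and some extra analysis; no new data are needed. The drawback is reliance on data being missing at random given what was observed. That is weaker than what the visit-wise or completer methods require, and the sensitivity analysis tests departures from it.
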